### Standard analgesia procedure

2.14.

Each participant will be given 200 mg of celecoxib orally the day before their surgery. Twenty minutes before the end of the operation, the anesthesiologist will administer 4 mg of ondansetron (Qilu Pharmaceutical Co., Ltd., Jinan, Shandong, China). After the procedure, a PCIA device will be connected, loaded with 100 μg of sufentanil (Yichang Renfu Pharmaceutical Co., Ltd., Yichang, Hubei, China), 8 mg of ondansetron, and 5 mg of butorphanol tartrate (Jiangsu Heng Rui Medicine Co., Ltd., Jiangsu, China), diluted to 100 ml with normal saline. The background PCIA dose will be 1 ml/h, the single press dose will be 2 ml, the locking time 15 min, and the maximum infusion rate is 10 ml/h.

In the post-anesthesia care unit (PACU), when the participant’s NRS is ≥4 points (i.e., they require analgesics), the anesthesiologist will administer 50 μg of fentanyl (Jiangsu Nhwa Pharmaceutical Co., Ltd., Xuzhou, Jiangsu, China) intravenously as remedial the analgesia. The subsequent dose will be half of that preceding, at a between-rescue analgesia dose interval of ≥20 min. When the NRS of the participant is <4 points, the remedial analgesia is considered effective. In the surgical ward, the participant will receive flurbiprofen axetil 50 mg (Beijing Taide Pharmaceutical Co., Ltd., Beijing, China) twice daily and acetaminophen oxycodone (Fujian Minglong Pharmaceutical Co., Ltd., Longyan, Fujian, China) three times daily as the basic analgesic. The standard of care is to initiate the remedial analgesia procedure when the participant’s NRS is ≥4, at which time they are administered an intravenous injection of 50 mg of pethidine (Qinghai Pharmaceutical Factory Co., Ltd., Xining, Qinghai, China), which can be repeated every 4–6 h, for a maximum daily dose of 300 mg. In case of moderate to severe nausea or vomiting after the operation, 4 mg of intravenous ondansetron will be administered.

## Outcomes

3.

### Primary outcome

3.1.

The primary trial outcome is incidence of rebound pain within the first 12 postoperative hours in the esketamine and placebo groups. Herein, rebound pain is defined as the transition from well-controlled pain (NRS ≤ 3) to severe pain (NRS ≥ 7) in participants undergoing TKA under regional block anesthesia.

### Secondary outcomes

3.2.

Incidence of rebound pain within the first 24 postoperative hours.Time to entering the first pain cycle during the first 24 postoperative hours (i.e., time from PACU transfer to initial analgesic intervention).Time to first rebound pain during the first 24 postoperative hours (i.e., time from PACU transfer to first NRS ≥ 7).The modified rebound pain score (MRPS). MRPS = HNRS−LoNRS (PACU) (2), where HNRS (24) is the highest NRS pain score within 24 h after regional nerve block, and LoNRS (PACU) is the lowest NRS pain score while in the PACU.NRS scores at rest (i.e., laying quietly) and exercise (i.e., raising the affected limb ≥5 times to ≥30 cm) at: 1 day before their operation, PACU transfer, the morning of the first postoperative day; during physical therapy on the first postoperative day; the evening of the first postoperative day; the morning of the second postoperative day; and the evening of the second postoperative day. Morning is defined as 8–10 a.m. and evening as 8–10 p.m.The cumulative opioids upon transfer to the PACU and at 12, 24, and 48 postoperative hours. Cumulative opioids includes administration of basic and remedial analgesics, which will be converted to ‘morphine-equivalent dose’ for analyzes.One day before their operation and first postoperative Timed Up and Go test (i.e., time required to stand up from a standard-height armchair, walk forward three meters, walk back to the chair, and sit down).Range of motion [i.e., degree of the affected knee joint from neutral (0°) to maximum flexion] of the active and passive knee joints at 1 day before their operation and on the first postoperative day.Time to discharge (i.e., when the participant can walk from bed to bathroom independently and along the corridor without the help of a walker).Length of stay (i.e., number of days from admission to discharge).Quality of Recover (QOR)-15 scores at 1 day before their operation and the first postoperative day.Blood glucose and cortisol concentration at admission and the first postoperative day.Patient satisfaction at discharge, where 1 point is ‘unsatisfactory’, 2 points is ‘relatively satisfactory’, and 3 points is ‘satisfactory’.

### Safety outcomes

3.3.

(1) nausea and vomiting; (2) respiratory depression (i.e., blood oxygen saturation < 93%); (3) hypertension (i.e., blood pressure > 30% of baseline value); (4) hypotension (i.e., blood pressure < 30% of baseline value); (5) tachycardia (i.e., heart rate > 100 beats/min); (6) bradycardia (i.e., heart rate < 50 beats/min); (7) nervous system complications (restlessness, delirium, nightmare, restlessness); (8)increased secretions; (9) nerve injury caused by regional block or local anesthetic poisoning; (10) wound infection, deep vein thrombosis, or pulmonary embolism.

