### Trial safety

3.4.

To ensure participant safety throughout the clinical trial, all inclusion and exclusion criteria will be strictly adhered to. The day before their operation, an investigator ([name]) will describe the study purpose and protocol, drug effects, potential benefits, possible toxic and side effects, and potential risks to the participant or their designated agent. Before participation, the research team will obtain the written informed consent of each participant to protect their legitimate rights and interests. Before starting this trial, the investigator will review the emergency plan for improvements and will communicate with multiple departments regarding adverse events (AE) that may occur in this clinical study to arrange protocols for their assistance in case of emergency. The nerve block technique is conducted under ultrasound guidance and is administered by an experienced expert. During and after the nerve block operation, participants will undergo ECG, blood oxygen, and blood pressure monitoring. The dose and concentration of esketamine administered to each study participant will be based on evidence-based standard of clinical care and drug manufacturer recommendations. A multifunction monitor will be used to monitor participants during surgery. All anesthesiologists participating in this trial have rich clinical experience, are skilled at handling critical events, and have received professional GCP training. The quality control nurse will check whether first aid drugs and materials are complete and within their periods of validity before the trial. Our medical institution has developed standard treatment and rescue procedures for adverse reactions caused by medications, including nausea and vomiting, psychiatric symptoms, and anaphylactic shock. In the PACU and surgical wards, participants will undergo continuous ECG, blood oxygenation, and blood pressure monitoring for at least 24 h. The Medical Ethics Committee and the Clinical Trial Safety Supervision Committee of Qingdao University will supervise the trial.

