Secondary outcomes will be exploratory, without adjustment for multiple comparisons. The first time to enter the pain cycle within the first 24 postoperative hours and the first time to rebound pain within the first 24 postoperative hours will constitute the survival data. Kaplan–Meier survival curves and log-rank tests will be used to analyze survival data, and univariate COX regression will be used to calculate HR and 95% CI. NRS and opioid use at different postoperative intervals will constitute repeated-measurement data. Generalized estimation equation (GEE) will be used, with patient identification number as the main variable, time as the main internal variable, and NRS and opioid consumption as the dependent variables. Independent samples *t*-tests or Mann–Whitney U tests will be used to compare independent data between the groups. The Hodges–Lehmann method will be used to evaluate the pseudo-median differences and 95% CI. Categorical data will be expressed as the number of cases (percentage) and analyzed using the chi-square test, Yate’s chi-square test, or Fisher’s exact probability test. Safety outcomes will be analyzed using the safety analysis dataset. All participants who undergo randomization and for whom post-trial safety evaluation data are available will be included in the safety analysis dataset. All statistical tests will be two-sided and *p* < 0.05 will be considered statistically significant.

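### As worded, the hypertension and hypotension safety outcomes share one cut-off at 30% of baseline pressure, where a rise or fall of more than 30% is probably meant

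*Protocol article*

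**What the plan says.** Section 3.3 of the protocol article lists ten safety items. Item (3) is "hypertension (i.e., blood pressure > 30% of baseline value" and item (4) is "hypotension (i.e., blood pressure < 30% of baseline value". They stand next to each other in the list, joined by "30% of baseline value); (4) hypotension (i.e., blood pressure". Neither item mentions a change, a rise or a fall, and no other section restates or clarifies them.

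Three other parts of the article bear on how the definitions would be used:

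- **Section 3.4 (Trial safety):** in the PACU and on the wards, "participants will undergo continuous ECG, blood oxygenation, and blood pressure monitoring for at least 24 h".
- **Section 7 (Statistical methods):** "Safety outcomes will be analyzed using the safety analysis dataset". Categorical data are compared by chi-square or Fisher-type tests.
- **Section 5 (Data management):** the eCRF is built from the protocol, and logical verification rules are configured in the data capture system and tested before use.

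**The concern.** A percentage of baseline and a percentage change from baseline are different quantities. The text gives the first, while the labels only make sense with the second. Because the same percentage appears on both sides with the sign reversed, the two definitions meet at a single point. Every reading falls into one class or the other, apart from one exactly at the cut-off.

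The neighbouring items point the same way. The saturation and heart-rate items are literal cut-offs, and the heart-rate pair (above 100, below 50 beats/min) leaves a normal band from 50 to 100. The blood-pressure pair leaves none. Someone who applied the list consistently would apply the 30% literally as well.

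At stake are two analysed safety outcomes in a trial that infuses esketamine after spinal anaesthesia. If the definitions were used as written, neither outcome could separate the arms. If staff each substituted their own reading, ascertainment would rest on individual interpretation instead of the stated rule.

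**Working it through.** **Inputs from the article.** Hypertension if BP > 30% of baseline; hypotension if BP < 30% of baseline (section 3.3). There are 178 participants per arm (section 2.6).

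**Inputs assumed.** The article gives no blood-pressure values. Baselines of 100 to 180 mmHg are used for illustration. The ratio R = BP / baseline is taken as Normal(m, s), with m = 0.8 to 1.0 and s = 0.10 to 0.20.

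**Step 1: the cut-offs.** The literal cut-off is 0.30 × baseline. On a change-from-baseline reading, the cut-offs are 1.30 × and 0.70 × baseline.

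| Baseline (mmHg) | Literal, both outcomes | Change reading, upper | Change reading, lower |
|---|---|---|---|
| 100 | 30 | 130 | 70 |
| 120 | 36 | 156 | 84 |
| 140 | 42 | 182 | 98 |
| 160 | 48 | 208 | 112 |
| 180 | 54 | 234 | 126 |

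**Step 2: what the literal rule does.** This step needs no assumed pressure.

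- R = 1.0 (no change): 1.0 > 0.30, so hypertension.
- R = 0.5 (a 50% fall): 0.5 > 0.30, so still hypertension.
- Hypotension needs R < 0.30, which is a fall of more than 1 − 0.30 = 70%.

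**Step 3: share of readings classified, literal rule.** P(hypertensive) = 1 − Φ((0.30 − m)/s).

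- m = 1.0, s = 0.10: z = −7.0, so essentially 100%.
- m = 0.8, s = 0.15: z = −3.33, so 99.957%, leaving 0.043% hypotensive.
- m = 0.8, s = 0.20 (the most extreme case): z = −2.5, so 99.38%, leaving 0.62% hypotensive.

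Over all nine combinations, 99.4% to 100% of readings are hypertensive and at most 0.6% hypotensive. In seven of the nine the hypotensive share is below 0.05%.

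**Step 4: the same distributions, change reading.** P(R > 1.30) runs from about 0% (m = 0.8, s = 0.10) to 6.7% (m = 1.0, s = 0.20). P(R < 0.70) runs from 0.1% (m = 1.0, s = 0.10) to 30.9% (m = 0.8, s = 0.20). Both outcomes could then differ between participants.

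**Step 5: from readings to participants.** The shares in steps 3 and 4 are per reading. With many readings each, a participant needs only one above 0.30 × baseline to be hypertensive. Literal use therefore gives about 178/178 in each arm and a risk ratio of about 1 whatever esketamine does. A hypotensive participant needs at least one fall of more than 70%. That count was not modelled, but such a fall would be exceptional.

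**The case against.** The strongest reply is that nobody will misread this. The labels, the mirrored signs and the shared percentage all suggest a rise or fall of more than 30%. Trained anaesthesiologists are unlikely to record a normal pressure as hypertension. Section 5 has the eCRF reviewed by the clinical project leader and the statistician and its logic tested online, and a rule that flagged every reading would be hard to miss there. Section 3.5 has the investigator record adverse events on a case report form, and nothing says these two outcomes are derived by algorithm from raw readings.

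Much of this stands. A reader might infer that the trial will in fact class everyone as hypertensive and miss any haemodynamic difference between the arms. The documents do not support that: no eCRF rule is shown, so the loss of information depends on literal coding or application.

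A reader might also want to fault the article for not naming the pressure (systolic or mean) or the baseline reading. A condensed article may leave that detail to the full protocol, so it is not part of this point. Nor does the article rank these two items above the other eight.

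What the reply does not do is make the text right. This is a definition that is stated and stated wrongly, not a detail left out. The intended meaning has to be guessed, and the eCRF is to be built from the protocol.

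**Conclusion.** The definitions of safety items (3) and (4) are wrong as written. That conclusion rests on the wording alone: one cut-off at 0.30 × baseline, no normal range, and hypotension only after a fall of more than 70%. The mmHg figures and the reading shares rest on the assumed baselines and ratio distributions and serve only to show scale.

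The consequence is conditional. If the wording were applied literally, two of the ten safety items would carry no between-arm information. The intent is very probably a change of more than 30% from baseline, but that is an inference for the sponsor to confirm. The primary outcome, the sample size and the other safety items are untouched. This is a wording error that should be corrected, not a flaw in the design.

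**What to change.** The sponsor should confirm what was meant. If it is a change from baseline, restate item (3) as blood pressure more than 30% above the baseline value and item (4) as blood pressure more than 30% below it. Use the same wording in the eCRF and its logical checks, and check any rule already configured against it. The cost is one sentence in section 3.3 and the matching eCRF rule. No analysis method or sample size changes.

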### Trial safety

3.4.

To ensure participant safety throughout the clinical trial, all inclusion and exclusion criteria will be strictly adhered to. The day before their operation, an investigator ([name]) will describe the study purpose and protocol, drug effects, potential benefits, possible toxic and side effects, and potential risks to the participant or their designated agent. Before participation, the research team will obtain the written informed consent of each participant to protect their legitimate rights and interests. Before starting this trial, the investigator will review the emergency plan for improvements and will communicate with multiple departments regarding adverse events (AE) that may occur in this clinical study to arrange protocols for their assistance in case of emergency. The nerve block technique is conducted under ultrasound guidance and is administered by an experienced expert. During and after the nerve block operation, participants will undergo ECG, blood oxygen, and blood pressure monitoring. The dose and concentration of esketamine administered to each study participant will be based on evidence-based standard of clinical care and drug manufacturer recommendations. A multifunction monitor will be used to monitor participants during surgery. All anesthesiologists participating in this trial have rich clinical experience, are skilled at handling critical events, and have received professional GCP training. The quality control nurse will check whether first aid drugs and materials are complete and within their periods of validity before the trial. Our medical institution has developed standard treatment and rescue procedures for adverse reactions caused by medications, including nausea and vomiting, psychiatric symptoms, and anaphylactic shock. In the PACU and surgical wards, participants will undergo continuous ECG, blood oxygenation, and blood pressure monitoring for at least 24 h. The Medical Ethics Committee and the Clinical Trial Safety Supervision Committee of Qingdao University will supervise the trial.

### Adverse event reporting

3.5.

AE in this trial include any adverse symptoms, abnormal physical signs, and abnormal experimental results after the intervention, regardless of whether there is a causal relation with the intervention. Any AE, including those described by the participant or obtained through investigator inquiry or physical examination, laboratory examination, or other examination methods, will be recorded, actively managed, and closely tracked until the condition is relieved or stable. The investigator will track all AE and record them in the standard paper case report form (CRF), including their detailed content, location, time, severity, treatment measures, and treatment results.

SAE refers to death, life-threatening, severe disability or loss of function, need for hospitalization or prolonged hospitalization, and other critical medical events after the participants receive the intervention. Should a SAE occur, all rescue efforts will be made and necessary measures taken to actively avoid permanent damage. The investigator will notify the person in charge, the clinical trial organization, and the ethics committee by telephone or fax within 24 h and record the SAE details in the CRF.

## Data collection

4.

An investigator ([name], [name], or [name]) will conduct a preoperative visit with eligible participants the day before their surgery. Baseline data, recorded from participant self-report and their electronic medical records, will include age, sex, height, weight, ASA grade, complications, duration of analgesic use, admission time, and preoperative blood glucose and cortisol concentration. The NRS will be used to assess baseline pain. The Timed Up and Go test will be used to evaluate baseline knee function and active and passive knee flexion. Preoperative baseline recovery quality score will be evaluated using the QOR-15. The anesthesiologist will collect and record intraoperative data through the anesthesia management system, including dosages of sedatives and analgesics, steroid use (yes/no), blood loss, infusion volume, tourniquet use time, operation time, and any AE. An investigator ([name], [name], [name], or [name]) will collect postoperative data, including pain-related indicators, opioid consumption, knee joint function recovery indicators, and any AE. Postoperative data will be collected from the doctor and nurse management stations of the hospital information system, standardized CRF, and PCIA information storage cards (Table 1). Outcome assessors will have been trained in the standard operating procedures of clinical drug trials. The clinical data monitoring committee (DMC) will supervise all data collection to ensure reporting accuracy, integrity, readability, and timeliness. All source files will be rigorously cleaned to ensure accurate data use.

**Table 1 tab1:** Study protocol.

Outcome measure	Visit 1	Visit 2	Visit 3	Visit 4	Visit 5	Visit 6	Visit 7
Time	1 day pre- surgery	During operation	PACU	Within 12 h post-surgery	POD 1	POD 2	Hospital discharge
Eligibility screening	X	–	–	–	–	–	–
Informed consent	X	–	–	–	–	–	–
Demographic characteristics	X	–	–	–	–	–	–
Preoperative education	X	–	–	–	–	–	–
Baseline measures	X	X	–	–	–	–	–
Randomization	X	–	–	–	–	–	–
Intervention	–	X	–	–	–	–	–
Incidence of rebound pain	–	–	–	X	X	–	–
First time to begin pain cycle	–	–	–	X	X	–	–
First time rebound pain occurred	–	–	–	X	X	–	–
NRS scores	X		X	X	X	X	–
Cumulative opioid consumption	–	X	X	X	X	X	–
Timed Up and Go test	X	–	–	–	X	–	–
Range of motion of knee joints	X	–	–	–	X	–	–
Time to reach discharge standard	–	–	–	–	–	–	X
Length of stay	–	–	–	–	–	–	X
Blood glucose and cortisol concentration	X	–	–	–	X	–	–
Patient satisfaction at discharge	–	–	–	–	–	–	X
Safety outcomes	Throughout the study period, until patient discharge						

NRS, numeric rating scales; POD, postoperative day.

## Data management

5.

An electronic data capture (EDC) system will be used for data management. The data management process will follow GCP for clinical drug trials and relevant national laws and regulations, guidelines, the data management plan (DMP), and appropriate data management standard operating procedures. The clinical research protocol stipulates that the data manager ([name]) will write the DMP to standardize the data management process. The DMP is a dynamic file that can be modified and updated according to the actual situation during the study. The electronic CRF (eCRF) will be designed by the data manager according to the clinical study protocol and reviewed by the clinical project leader ([name]) and the statistician. These professionals will be responsible for setting up the EDC database and configuring logical verification rules. After the configuration is completed, study professionals will conduct online tests, including data entry, data export, logical check tests, eCRF interface tests, and system function tests, to confirm the accuracy and rationality of the database structure and input page. The data manager will write a data verification plan according to the clinical study protocol and eCRF.

Before data entry, the data manager will train relevant personnel on using the uniform EDC. The clinical research coordinator (CRC) authorized by the project leader will log into the EDC through an independent account and enter the participant’s data according to study protocol. All data will be verified for accuracy. Timely data entry and backup will be maintained throughout the clinical research data management process. The database will be deployed on the Ali Cloud server, with automatic daily backups at a fixed time. After data cleaning, the data manager will write a data review report and then organize all investigators, clinical project leaders, and statisticians for a data review meeting and confirm dataset divisions. Any data problems will be efficiently corrected by the responsible person. After verifying that all lock list items are complete, all investigators, clinical principals, data managers, and statisticians will sign the lock approval document, and the database will be locked. All necessary records will be kept in a secure, confidential location, readily available for access and inspection by relevant authorities.

